### Secondary outcome analyses

Logistic and linear regression analyses will be performed for dichotomous and continuous secondary outcomes, respectively. Regression analyses will be adjusted for GA and admitted centre. Survival analyses using Cox proportional hazards regression will be performed to investigate the relations between the outcomes time to intubation, time to discharge, and time to death. Cause-specific risk models will be computed to consider death as competing risk for severe disabilities. This is done by estimating cumulative incidence functions using the Fine and Grey model [39].

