### Study participants

Patients are eligible for inclusion if the following criteria are met: (1) GA at birth below 29 weeks, (2) postnatal age of at least 120 h, (3) adequately dosed caffeine (max 50% increase above standard daily maintenance dose), (4) non-invasive respiratory support according to the local treatment policy, (5) frequent and/or severe apnoea that require a medical intervention as judged by the attending physician (indication to start doxapram, to provide additional caffeine or to start mechanical ventilation if not included in the trial) and (6) written informed consent of parents or legal representatives. A pragmatic study design is chosen, because we anticipate considerable variation between centres and physicians in the judgment on what frequency and duration of apnoea is considered unacceptable and requires intervention.

Exclusion criteria are as follows: (1) previous use of open label doxapram, (2) use of theophylline to replace doxapram, (3) chromosomal defects, (4) major congenital malformations that compromise lung function resulting in chronic ventilation, or increase the risk of death or adverse neurodevelopmental outcome and (5) palliative care or treatment limitations because of high risk of impaired outcome.

Several conditions, such as sepsis, pneumonia, necrotizing enterocolitis (NEC) and patent ductus arteriosus may present with apnoea and respiratory failure. Distinction from apnoea caused by prematurity is difficult or even impossible. Therefore, the suspicion of one of these diagnoses is not considered an exclusion criterion. However, the diagnosis may result in a decision to primarily intubate the infant and not include the patient in the trial at that time point. This decision is left to the attending physician and medical team. Discontinuing study medication is always allowed if judged necessary by the attending physician and medical team, although discouraged to prevent more open label treatment in the placebo group.

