#### Secondary outcomes

Secondary outcomes with details on the statistical analyses are summarized in Table 1.

**Table 1 Tab1:** Summary of the secondary objectives with the statistical analysis and time of measurement

	**Secondary outcomes**	**Details of statistical analysis**^**a**^	**Time of measurement**
**Short-term mortality and comorbidity**	- Bronchopulmonary dysplasia (NICHD criteria) - Death	Logistic regressions will be performed, corrected for GA and centre, for BPD and death separately, and the combined outcome of BPD and death. Survival analysis will be performed for time to death. Cause-specific risk models will be computed to consider death as competing risk for severe disabilities at 18 to 24 months of age.	Postmenstrual age of 36 weeks and hospital discharge
	**Admission:** - Length of stay intensive care - Length of stay hospital	Survival analyses will be performed for time to discharge.	Hospital discharge
	**Respiration:** - Incidence of endotracheal intubations - Number of days on invasive ventilation - Number of days on respiratory support - Number of days with supplemental oxygen - Respiratory complications - Use of postnatal corticosteroids	Logistic regression analysis will be performed for the dichotomous respiratory complications and the use of corticosteroids. Linear regression analysis will be performed for the incidence of endotracheal intubations, and number of days on invasive ventilation, respiratory support, and supplemental oxygen. In both analyses will be corrected for GA and centre. A survival analysis will be performed for the time to intubation.	Hospital discharge
	**Gastro-intestinal:** - Solitary intestinal perforation - Necrotizing enterocolitis > stage 2 (Bell’s criteria) - Feeding problems (days with parental feeding after inclusion) - Body weight - Head circumference	Logistic regression analysis will be performed for SIP, NEC and feeding problems. Linear regression analysis will be performed for body weight and head circumference. Both analyses will be corrected for GA and centre.	Hospital discharge
	**Neurological:** - Intravenous haemorrhage - Clinical seizures - Periventricular leukomalacia	Logistic regression analysis will be performed for all neurological outcomes, corrected for GA and centre.	Hospital discharge

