#### Randomization and blinding

Participants will be randomly allocated in a 1:1 ratio, stratified according to study centre and gestational age (<26 weeks or ≥26 weeks), and using random permutated blocks. Multiple birth infants will be randomized independently, unless parents or legal representatives explicitly request that siblings are to be allocated to the same treatment arm. Randomization and drug supply management is performed via an electronic online platform (ALEA®, FormsVision BV, Abcoude, the Netherlands).

Once the participant has been randomized, a study medication kit will be allocated. All treatment kits will be visually identical and contain either doxapram or placebo. The clinical trial centre and trial pharmacy of the Erasmus Medical Centre will manage the randomization list. The parents, researchers and medical team will have no access to the randomization list. Unblinding is only performed by an independent safety officer in emergency situations where knowledge of the study drug is considered absolutely necessary for the clinical management of the included patient.

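### Age at randomisation is missing from the secondary duration and time-to-event models: an optional efficiency gain of unknown size, not an error

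*Protocol article*

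**What the plan says.** The Secondary outcome analyses section sets one covariate rule: "Regression analyses will be adjusted for GA and admitted centre". Table 1 repeats it for the respiratory outcomes, where "Linear regression analysis will be performed for the incidence of endotracheal intubations, and number of days on invasive ventilation, respiratory support, and supplemental oxygen", corrected for the same two factors. For admission outcomes the table says only that "Survival analyses will be performed for time to discharge". That row names no covariates, but the text of the section makes these Cox regressions, so the general rule presumably covers them.

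The two covariates match the randomisation strata (centre, and gestational age split at 26 weeks). Under Study participants, entry requires "GA at birth below 29 weeks" and "postnatal age of at least 120 h". No upper postnatal age is given. Infants enter when the attending physician judges that apnoea needs intervention, and the protocol expects that judgement to vary between centres and physicians.

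Age at randomisation appears in no listed model. It is also absent from the additional primary-outcome model, which adds sex, intraventricular haemorrhage and being small for gestational age to the stratification factors.

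The protocol does not say whether respiratory days and length of stay are counted from birth, admission or randomisation. In Table 1 only parenteral feeding days and meningitis are tied to inclusion.

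**The concern.** Gestational age at birth does not tell how mature an infant is on the day of randomisation when entry can happen at any age from day 5 onward. An infant randomised later is closer to the maturity at which support ends and discharge follows. If days are counted from randomisation, entry age is in effect subtracted from the outcome, and it should then predict the days that remain. Leaving it out puts that variation in the residual of the linear models and makes it an omitted prognostic covariate in the Cox models.

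What is at stake is power for a handful of secondary outcomes. The primary analysis and the sample size are not affected. The covariate comes almost free: applying the 120 h criterion already requires the age of every infant at entry.

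**Working it through.** The plan gives no figure for this point, so there is none to reproduce. Its sample size (198 per arm) concerns the primary outcome and serves here only as a base.

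**Inputs.** From the protocol: 198 infants per arm, 1:1 allocation, covariates gestational age and centre, entry from 120 h. Assumed, because the protocol gives neither: the SD of entry age, and the SD of the outcome that remains after gestational age, centre and entry age.

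**Linear models, days counted from randomisation.** Suppose days = (age at exit) − (age at entry), with age at exit independent of entry age given gestational age. The slope on entry age is then −1, and

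- share of residual variance removed: R² = SD_entry² / (SD_entry² + SD_rest²)
- reduction in standard error: 1 − √(1 − R²)

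| SD entry (days) | SD rest (days) | R² | SE reduction |
|---|---|---|---|
| 3 | 40 | 9/1609 = 0.006 | 0.3% |
| 6.5 | 24.5 | 42.25/642.5 = 0.066 | 3.3% |
| 7 | 30 | 49/949 = 0.052 | 2.6% |
| 10 | 30 | 100/1000 = 0.100 | 5.1% |
| 10 | 17.5 | 100/406.25 = 0.246 | 13.2% |
| 14 | 20 | 196/596 = 0.329 | 18.1% |
| 12 | 14 | 144/340 = 0.424 | 24.1% |

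In sample-size terms, 198/(1 − R²) gives 200, 208, 220 and 248 per arm at R² of 0.01, 0.05, 0.10 and 0.20. A comparison with 80% power would move to Φ(2.802/√(1 − R²) − 1.960) = 80.4%, 82.0%, 84.0% and 87.9%.

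**Sensitivity to the two structural assumptions.**

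- *Slope.* Infants who still need intervention at a later age may also come off support later. If each day of later entry goes with half a day of later exit, the slope is −0.5. At SDs of 10 and 17.5 days, R² falls from 0.246 to 25/(25 + 306.25) = 0.075, and the SE reduction falls from 13.2% to 3.8%. If it goes with a full day, the gain is zero.
- *Time origin.* If days run from birth, entry age drops out of the outcome. With exit independent of entry age, R² = 0.

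**Cox, logistic and linear models by simulation.** 396 infants, 600 replicates, one standardised baseline covariate, no censoring, robust standard errors for the linear model. Each cell shows the result without → with the covariate.

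| Model | Covariate effect per SD | Mean estimate | Mean SE | Power |
|---|---|---|---|---|
| Linear | 0.2 | 0.247 → 0.247 | 0.1024 → 0.1006 | 67% → 69% |
| Linear | 0.5 | 0.255 → 0.254 | 0.1126 → 0.1011 | 63% → 71% |
| Cox | 0.2 | 0.281 → 0.292 | 0.1020 → 0.1023 | 78% → 79% |
| Cox | 0.5 | 0.236 → 0.284 | 0.1016 → 0.1023 | 64% → 81% |
| Logistic | 0.2 | 0.585 → 0.594 | 0.2039 → 0.2057 | 82% → 82% |
| Logistic | 0.5 | 0.577 → 0.611 | 0.2039 → 0.2108 | 78% → 82% |

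In the linear model the estimate stays put and the SE shrinks. In the Cox and logistic models the SE does not shrink. The coefficient moves away from zero, and power rises noticeably only when the covariate is strong. Simulation error on a power near 80% is √(0.8 × 0.2/600) = 1.6 percentage points, so one-point differences mean little.

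**The case against.** The strongest reply is that nothing here is wrong. Adjusting for the stratification factors is coherent and accepted, allocation is randomised, and extra covariates for secondary outcomes are a matter of choice. That stands, and it is why this point is optional.

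Four stronger readings are tempting, and the documents support none of them.

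- *That a chance imbalance in entry age would pass for a treatment effect.* Randomisation keeps the estimates valid, and chance imbalance is already reflected in the standard error. Prespecifying the covariate would only forestall a later argument about such an imbalance.
- *That the gain is large.* With entry-age SDs of 6.5 to 12 days, remaining SDs of 2 to 3.5 weeks and independence, one gets 7–42% of residual variance, or 1/(1 − R²) − 1 = 7–74% more infants. None of those inputs is in the protocol, and 7% is not a floor: other spreads, a shallower slope or counting from birth bring the gain close to zero.
- *That every model loses precision.* This is so only for the linear models. In Cox and logistic models the adjusted and unadjusted ratios are different quantities, and the cost of omission is attenuation and power.
- *That every secondary model needs the covariate.* The argument concerns durations and times that run from entry. No gain is shown for retinopathy, hearing loss, enterocolitis, growth or behaviour. The model of exit from support does not describe ventilation days closely either, so the gain there is the least certain of the outcomes named in the fix.

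What remains is that the covariate set is written into the protocol rather than left open, and that the primary outcome already has an additional model with prognostic covariates. Infants must also be on non-invasive support at entry, so time to intubation naturally starts at randomisation.

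**Conclusion.** The point holds as an optional improvement. The secondary duration and time-to-event models leave out maturity at entry, although entry age is open-ended and known for every infant. The current comparisons are unbiased and need no correction.

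The size cannot be derived from the documents. For linear models of days counted from randomisation, the SE reduction lies between under 1% and roughly 18–24%, given entry-age SDs of 3 to 14 days, remaining SDs of 14 to 40 days and a slope of −1. It is smaller with a shallower slope. It is about nil if days run from birth under the same independence assumption. For Cox models, power at a log hazard ratio of 0.28 is practically unchanged with a weak covariate and rises from 64% to 81% with a strong one. Which of these applies here is unknown. The unstated time origin matters as much as the covariate, because it decides whether there is anything to gain.

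**What to change.** For days on respiratory support, on supplemental oxygen and on invasive ventilation, for length of stay or time to discharge, and for time to intubation:

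1. State that counting starts at randomisation.
2. Add postnatal age at randomisation (days, continuous) beside gestational age and centre, and say that the Cox models carry the same covariates.

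Leave the remaining secondary models as they are, especially those for rare binary outcomes. Settle the wording before unblinding.

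The cost is a line or two of text and one degree of freedom per model, with no new data. The adjusted hazard ratios become conditional on entry age, and the report should say so.

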#### Primary outcome

The primary outcome is the composite outcome of death or severe disability at 18 to 24 months corrected age.

Severe disability will be defined as having one or more of the following outcomes at the age of 18 to 24 months: cognitive delay, cerebral palsy, severe hearing loss, or bilateral blindness. Cognitive delay will be defined as a Mental Development Index score of less than 85 on the Bayley Scales of Infant and Toddler Development III [27]. Cerebral palsy will be diagnosed if the patient had a non-progressive motor impairment, characterized by abnormal muscle tone and decreased range or control of movements. The level of gross motor function will be determined with the Gross Motor Function Classification System and is defined as severe movement disability if the score is > level 2 [28].

Severe hearing loss will be defined as hearing loss requiring hearing aids and will be measured by audiometry in patients with signs of hearing abnormalities at the corrected age of 18 to 24 months [29]. Hearing will be assumed to be normal in participants with a normal hearing screening after birth and no signs of hearing abnormalities at the corrected age of 18 to 24 months. Severe visual impairment or blindness will be defined as a corrected visual acuity less than 20/200 [30].

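### The competing-risk model for severe disability is a time-to-event model for an outcome that is read once, at the 18 to 24 month assessment, and has no event time

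*Protocol article*

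**What the plan says.** Under Secondary outcome analyses the protocol states "Cause-specific risk models will be computed to consider death as competing risk for severe disabilities", and the next sentence explains how: "This is done by estimating cumulative incidence functions using the Fine and Grey model". Table 1, in the row on short-term mortality and comorbidity, announces the same analysis without naming Fine-Gray: "Cause-specific risk models will be computed to consider death as competing risk for severe disabilities at 18 to 24 months of age".

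The outcome is defined under Primary outcome: "Severe disability will be defined as having one or more of the following outcomes at the age of 18 to 24 months". The components are cognitive delay, cerebral palsy, severe hearing loss and bilateral blindness. Cognitive delay is a test score below a cut-off: "Cognitive delay will be defined as a Mental Development Index score of less than 85". No date of onset is defined for any component.

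For outcomes that do have dates, Table 1 says "Survival analyses will be performed for time to discharge" and "A survival analysis will be performed for the time to intubation". The secondary outcome section assigns Cox regression to these and to time to death.

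**The concern.** A Fine-Gray model regresses the subdistribution hazard of an event over time, so it needs to know when the event happened. A Bayley score below the cut-off does not happen on a date; it is found on the day the child is tested. The only available time is therefore the visit date, which reflects scheduling within a six-month window and not the course of disease.

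If that timing is set aside, what remains is a binary comparison with the dead counted as not disabled. An arm with more deaths then has fewer infants who can be found disabled. The hazard ratio could be read as a statement about disability when part of it is a statement about mortality. This matters because the trial's stated equipoise sets possible benefit against concern about brain development, and readers will look for disability separately from death.

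**Working it through.** The protocol gives no figure for this analysis, so there is none to reproduce.

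**1. Timing.** Death has a date. Severe disability has only the date of the assessment. Two children with the same impairment, seen at 18 and at 24 months, would enter as early and late events although nothing about the disability differs.

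**2. What the model reduces to.** Suppose all disability is recorded at one common age, after the deaths, with complete follow-up. Infants who died stay in the Fine-Gray risk set. The subdistribution hazard ratio is then a complementary log-log comparison of P = probability of being alive and disabled, among all randomised:

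- P = (1 − mortality) × (disability risk among survivors)
- ratio = ln(1 − P₁) / ln(1 − P₀)

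**3. Numbers.** Both mortality and disability among survivors are assumptions. Take 40% disability among survivors in both arms, so that survivors do not differ.

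| Mortality, arm 1 vs arm 0 | P₁ | P₀ | Ratio |
|---|---|---|---|
| 20% vs 10% | 0.80 × 0.40 = 0.32 | 0.90 × 0.40 = 0.36 | ln 0.68 / ln 0.64 = 0.864 |
| 15% vs 10% | 0.85 × 0.40 = 0.34 | 0.36 | ln 0.66 / ln 0.64 = 0.931 |

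With 35% disability among survivors and mortality 20% vs 10%, P is 0.28 vs 0.315 and the ratio is ln 0.72 / ln 0.685 = 0.87. With the arms reversed it is 1.15: an arm that saves lives appears to have more disability.

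**4. Using visit dates.** In a simulation with 200,000 infants per arm, visits were spread evenly over 18 to 24 months, disability was 35% of survivors in both arms, and mortality was 20% vs 10%. The ratio was 0.86 when undisabled children stayed in the risk set to the end of the window, and 0.77 when they left at their own visit. The 0.77 keeps the dead at full weight throughout; the usual censoring weights bring it back towards the single-visit value. The convention for visit dates can therefore move the result although no child's status has changed.

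**5. Precision.** At 198 per arm with complete follow-up, the approximate 95% interval is 0.61 to 1.22 for the 0.86 example (z = −0.84) and 0.67 to 1.30 for the 0.93 example (z = −0.42). Each shift is less than one standard error.

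**6. The same example as three categories.** At 20% vs 10% mortality, the dead / alive disabled / alive not disabled split is 20/32/48% against 10/36/54%. The odds ratio for disabled versus not disabled is (32/48)/(36/54) = 1.00. For dead versus alive not disabled it is (20/48)/(10/54) = 2.25. The whole difference appears under death, where it belongs.

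**The case against.** **The label.** A reader might infer that the protocol mistakes Fine-Gray for a cause-specific hazard model. The text says cause-specific risk, not hazard. That phrase can mean the cumulative incidence, which is what the following sentence describes. The wording is ambiguous and worth clarifying, but it is not a proven error.

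**The dead in the risk set.** A reader might infer that the analysis would hide deaths behind a false benefit. Keeping deaths in the risk set is a property of the estimand, and it preserves the comparison of all randomised infants. Deaths are not hidden: they count in the primary composite, have their own logistic and time-to-death analyses, and fall under an interim rule requiring an absolute difference of at least 10% and p < 0.05. The 20% vs 10% example sits at that margin: 30 vs 15 neonatal deaths among 300 infants gives a Fisher p of 0.023. A 15% vs 10% difference falls short of it. What stands is that the single disability ratio mixes the two effects and cannot be read alone.

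**Cox regression.** A reader might infer that Cox is wrong for time to intubation and time to discharge because death precludes both. The documents do not support that. Cox with deaths censored is a valid cause-specific hazard analysis, the coding of deaths may be in a statistical analysis plan that is not shown, and Table 1 also compares continuous outcomes such as length of stay directly. Replacing Cox by Fine-Gray for intubation would bring in the same dependence on mortality. In a simulation with equal intubation hazards and a doubled death hazard, Cox gave 1.00 and Fine-Gray 0.94.

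**Time scale.** It can be said that fixing a common age is a detail for the analysis plan. With a common age, however, the model is a binary regression and should be specified as one.

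**Conclusion.** The point holds for severe disability: the protocol assigns a time-to-event model to an outcome that, by its own definition, has no event time. The estimate either depends on appointment dates or is a binary comparison of alive and disabled that moves with mortality. Under the assumed rates, with no difference among survivors, it would read about 0.86 at 20% versus 10% mortality and 0.93 at 15% versus 10%. These sizes are illustrations, since the protocol gives no mortality rates, and they are small against the trial's precision. The reason to change the model is that its result has no clear meaning, not that it would probably produce a significant false finding. This is a secondary analysis; the primary logistic analysis counts death as failure and is unaffected.

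**What to change.** Replace the Fine-Gray model for severe disability, in Secondary outcome analyses and in Table 1, with one of the following:

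- a multinomial model for dead / alive with severe disability / alive without severe disability, adjusted for gestational age and centre, with all three proportions shown by arm; or
- separate logistic regressions for death and for severe disability among survivors, with the same adjustment. The second must be labelled as conditional on survival and not a fully randomised comparison. The multinomial contrast of disabled versus not disabled needs the same caution.

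The primary analysis already plans to combine small centres, and a similar rule will be needed here. If a competing-risk term is kept anywhere, state whether it means a cause-specific hazard or a cumulative incidence.

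Optional: keep Cox for time to intubation and time to discharge, name the estimates as cause-specific hazard ratios if deaths are censored, and show the cumulative incidence of intubation and of discharge alive with death as the competing event.

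The cost is a change of wording before unblinding and a little programming. No new data are needed.
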